## Abstract

**Background:**

Alemtuzumab (Lemtrada®) is a newly approved therapeutic agent for relapsing-remitting multiple sclerosis (RRMS). In previous phase II and III clinical trials, alemtuzumab has proven superior efficacy to subcutaneous interferon beta-1a concerning relapse rate and disability progression with unprecedented durability and long-lasting freedom of disease activity. The humanized monoclonal antibody targets CD52, leading to a rapid and long-lasting depletion, especially of B and T cells. Arising from hematopoietic precursor cells a fundamental reprogramming of the immune system restores tolerogenic networks effectively suppressing autoimmune inflammatory responses in the central nervous system (CNS). Despite its favourable effects alemtuzumab holds a severe risk of side effects with secondary autoimmunity being the most considerable. Markers for risk stratification and treatment response improving patient selection and therapy guidance are a big unmet need for MS patients and health care providers.

**Methods/design:**

This is a mono center, single arm, explorative phase IV study including 15 patients with highly active RRMS designed for 3 years. Patients will be studied by a high-resolution analysis comprising a repertoire of various immunological assays for the detection of immune cells and their function in peripheral blood as well as the cerebrospinal fluid (CSF). These assays encompass a number of experiments investigating immune cell subset composition, activation status, cytokine secretion, migratory capacity, potential neuroprotective properties and cytolytic activity complemented by instrument-based diagnostics like MRI scans, evoked potentials and optical coherence tomography (OCT).

**Discussion:**

Our study represents the first in-depth and longitudinal functional analysis of key immunological parameters in the periphery and the CNS compartment underlying the fundamental effects of alemtuzumab in MS patients. By combining clinical, experimental and MRI data our study will provide a deeper understanding of alemtuzumab’s mechanisms of action (MOA) potentially identifying immune signatures associated with treatment response or the development of secondary autoimmunity. After validation in larger cohorts this might help to improve efficacy and safety of alemtuzumab therapy in RRMS patients.

**Trial registration:**

NCT02419378 (clinicaltrials.gov), registered 31 March 2015.

**Electronic supplementary material:**

The online version of this article (doi:10.1186/s12883-016-0556-9) contains supplementary material, which is available to authorized users.

## Background

Approximately 2.5 million people around the world suffer from multiple sclerosis (MS) [1], a chronic inflammatory disorder of the central nervous system (CNS). Inflammation, demyelination, and axonal degeneration are distinctive features of the pathological mechanism [2]. Its clinical course is typically characterized by initial episodes of transient neurological deficits with full or partial recovery (relapsing-remitting MS); over the time deficits may cumulate to increasing disability. With the development of new therapeutic agents treatment goals are changing from solely stabilizing to reversing the disease.

Alemtuzumab is a new promising therapy for RRMS, which might be able to fulfil this aim. Alemtuzumab has been approved by the EMA (European Medicines Agency) in September 2013 and the FDA (U.S. Food and Drug Administration) in November 2014 for the treatment of RRMS under the name Lemtrada®. It is a humanized monoclonal antibody targeting CD52 primarily expressed on T- and B-lymphocytes, and to lesser extents on dendritic cells, monocytes and macrophages [3]. Alemtuzumab leads to a rapid and significant depletion of CD52 expressing cells by antibody-dependent cell-mediated and complement-dependent cytotoxicity [4, 5]; hematopoietic precursor cells are not affected. Subsequent to depletion a slow repopulation starts arising from hematopoietic precursor cells following a distinct pattern. B cells repopulate rapidly within 6 months with predominating immature B cells, prolonged CD27^+^ memory B cell lymphopenia and increased serum levels of BAFF (B cell activating factor) [6]. In contrast, CD4^+^ and CD8^+^ lymphocytes do not recover to the lower limit of normal (LLN) before 35 or 20 months respectively post treatment [7]. CD4^+^ memory cells predominate in the CD4^+^ cell population probably based on homeostatic proliferation of cells that escaped depletion. Similarly, CD4^+^CD25^high^CD127^dim/-^ regulatory T cells (Treg) are found to be relatively upregulated 9 months after alemtuzumab treatment [7, 8]. In contrast, the proportion of proinflammatory cell-types such as T helper (T_h_) 1 and T_h_ 17 cells and the serum levels of their respective cytokines are reduced [9]. The reduced levels of circulating B and T cells after alemtuzumab treatment accompanied by successive repopulation restoring immune tolerance networks are assumed to underlie its strong anti-inflammatory effects in multiple sclerosis.

Several previous studies have proven high efficacy of alemtuzumab in early stages of multiple sclerosis before the course of pathophysiological events causes permanent CNS damage. In initial studies with secondary progressive MS (SPMS) patients alemtuzumab was not able to slow disease progression indicating a clear window of therapeutic opportunity in early disease stages [10–13]. Therefore, the following clinical development program included only RRMS patients.

The Phase 2, randomized, comparator-controlled study of treatment-naïve patients with early, active RRMS, CAMMS223 showed that patients treated with alemtuzumab (12 and 24 mg dose groups pooled) experienced a 74 % reduction in the risk for relapse (*p* < 0.001) and a 71 % reduction in the risk for sustained accumulation of disability (SAD; defined as an increase of 1.5 points for patients with a baseline score of 0 and of at least 1.0 point for patients with a baseline score of 1.0 or more for at least 6 months) (*p* < 0.001) compared to patients treated with subcutaneous (sc) IFNb-1a. Alemtuzumab patients also experienced a significant reduction in lesion burden (T2 weighted magnetic resonance imaging [MRI] findings) compared with sc IFNb-1a patients (*p* = 0.005). Moreover, EDSS (Expanded Disability Status Scale) scores improved by 0.39 points in alemtuzumab patients but worsened by 0.38 points in the IFNb-1a patients (*p* < 0.001) [14]. A post-hoc analysis demonstrated that even patients without clinical activity of MS before or during the trial showed improved EDSS scores and prompted hypotheses on an active neuroprotective potential of alemtuzumab [15].

The two phase 3 trials CARE-MS I [16] and CARE-MS II [17] again compared alemtuzumab with IFNb-1a therapy sc and included treatment-naive or pre-treated RRMS patients. Most of the results of CAMMS223 were confirmed. Alemtuzumab demonstrated a superior reduction of clinical relapse activity, with a risk reduction of 54.9 % in CARE-MS I and 49.4 % in CARE-MS II. However, only in CARE-MS II (42 % decreased risk; 21.1 % with IFNb-1a versus 12.7 % with alemtuzumab) but not in CARE-MS I (11 % with IFNb-1a versus 8 % with alemtuzumab) a significant reduction in the risk for SAD was observed.

Meanwhile, long-term data from on-going extension studies of patients from Phase II and III trials have been published confirming previous observations. The 5-year follow-up of CAMMS223 showed sustained beneficial effects on relapse rate and disability without almost any MRI alterations. Reduction in annual relapse reduction (ARR) by 69 % (*p* < 0.0001) was observed as well as reduction in SAD by 72 % (*p* < 0.0001) with stable or improved EDSS scores in 74 % of patients [17]. Recent 4-year follow-up data from CARE-MS extension studies demonstrated that 50–60 % of patients showed no evidence of disease activity (NEDA), which was defined as absence of clinical disease and MRI activity, in years 3 and 4. After the initial two treatment courses 36 % of patients in CARE-MS I and 32 % of patients in CARE-MS II required retreatment over 3 years, whereas 2–5 % of patients received other disease-modifying therapies (DMT) [18, 19]. Furthermore, the 4-year follow-up of CARE-MS II demonstrated favourable effects on disability with 6-month sustained reduction in disability (SRD, defined as a reduction in the EDSS score of either ≥1.0 or 0.5, for baseline EDSS scores below and above 5.5 for at least 6 months) in 41 % of patients and 12-month SRD in 30 % over 4 years [20]. Around 70 % of patients were free of any MRI disease activity at years 3 and 4 [21, 22]. Patients switched from IFNb-1a to alemtuzumab, experienced substantial improvements in clinical as well as MRI parameters [23–27].

However, the advantages of alemtuzumab are opposed by considerable side effects. Alemtuzumab was associated with secondary autoimmunity in all mentioned and previous studies. Thyroid adverse events were most common (18 % in CARE-MS I, 17 % in CARE-MS II, 26 % in CAMMS223, 41 % in the 7-year follow-up of the Cambridge-group) [16, 17, 28]. Immune thrombocytopenic purpura (ITP) (1–3 %) and anti-glomerular basement membrane disease (<1 %, anti-GBM, also known as Goodpasture’s syndrome) were also observed. More frequently, higher rates of infections (66 %), especially mild to moderate upper and lower airway infections, and infusion-associated reactions (IAR) (90 %) occurred in alemtuzumab treated patients [14, 16, 17]. The experiences of these trials led to the implementation of an extensive surveillance program allowing for early recognition and therapy of adverse events.

Although alemtuzumab is a promising and valuable new therapy for RRMS, its long-lasting potentially irreversible effect and the risk of severe side effects demand reliable markers for risk stratification and treatment response improving patient selection and therapy guidance. Thus, it is indispensable to shed more light on the still not fully understood MOA [29].

## Methods/design

### Study design

ALAIN01 is a single center, single arm, explorative phase IV study to elucidate further insights into the MOA of alemtuzumab treatment in 15 patients with RRMS. The study center is the Department of Neurology at the University Hospital Münster, Germany. Recruitment started in May 2015.

After a screening period of at most 28 days, eligible patients will start investigational treatment. The study is designed for 3 years and efficacy and safety measures are assessed on at least half-yearly visits. Additionally, blood and urine samples will be collected monthly to monitor for autoimmune diseases, which may be carried out by a local physician.

As required by the summary of product characteristics (SmPC) for Lemtrada®, patients will be advised to continue monitoring for late undesirable effects of Lemtrada® after termination of study participation. The study site will provide post-study patient care but also support continuation of medical attendance by a resident neurologist of the patient’s choice.

The clinical study is registered at clinicaltrials.gov (NCT02419378). It will be performed in accordance with the approval of the local ethics committee (Ethik-Kommission der Ärztekammer Westfalen-Lippe und der Westfälischen Wilhelms-Universität Münster, 2014-545-f-A), the requirements of the current German drug law (“Arzneimittelgesetz”), the current legal provisions regarding data protection, and the principals of Good Clinical Practice.

All participants are obliged to hand in the signed informed consent form (ICF).

### Patient population and selection

Patients with highly active RRMS will be included in the study. The below eligibility criteria imply, that they are indicated to receive alemtuzumab irrespective of study participation.

Patients who do not meet all the inclusion criteria in Table 1 or meet one of the exclusion criteria mentioned in Table 2 will be excluded from further study participation. Patients will also be excluded if treatment with alemtuzumab has not been started within 28 days after signing the informed consent form. Reasons for exclusion will be recorded in the CRF. Excluded patients may be re-screened at a later time.

**Table 1 Tab1:** Inclusion Criteria

Patients must meet all of the following criteria to be eligible for further study participation:	
1. Signed informed consent form (ICF)	
2. Age 18 to 55 years old (inclusive) as of the date the ICF is signed	
3. Diagnosis of MS according to the McDonald criteria 2010 and cranial MRI scan demonstrating white matter lesions attributable to MS within 10 years before screening	
4. Onset of MS symptoms (as determined by a neurologist, either at present or retrospectively) within 10 years of the date the ICF is signed	
5. EDSS score 0.0 to 5.0 (inclusive) at Screening	
6. Patients with (highly) active RRMS disease course indicated to receive alemtuzumab according to the following conditions (at least 1 out of 3 conditions has to be fulfilled):	
1. ≥2 MS relapses within 24 months	
2. Clinical (≥1 relapse) or MRI (new gadolinium enhancing lesions) disease activity under therapy with other disease-modifying therapies	
3. Severe relapse with high disease activity (≥9 T2 hyperintense Lesions and ≥1 gadolinium enhancing lesion) on MRI.	
7. Completion of all vaccinations required by the applicable immunization guidelines published by “ständige Impfkommission” (STIKO)	
8. History of chickenpox or positive test for antibodies against varizella zoster virus (VZV)

**Table 2 Tab2:** Exclusion Criteria

Patients will be excluded from this study if they meet any of the following exclusion criteria:	
1. Participation in another clinical trial at present or within 4 weeks of study entry. There may be exceptions at the discretion of the Investigator.	
2. Has any progressive form of MS	
3. Hypersensitivity to the active substance, or to any of the excipients of Lemtrada®	
4. Medical, psychiatric, cognitive, or other conditions that, in the Investigator’s opinion, compromise the patient's ability to understand the patient information, to give informed consent, to comply with the trial protocol, or to complete the study	
5. Any disability acquired from trauma or another illness that could interfere with evaluation of disability due to MS	
6. Major systemic disease or other illness that would, in the opinion of the Investigator, compromise patient safety or interfere with the interpretation of study results, e.g., current peptic ulcer disease or other conditions that may predispose to haemorrhage	
7. Known bleeding disorder (e.g., dysfibrinogenemia, factor IX deficiency, haemophilia, Von Willebrand’s disease, disseminated intravascular coagulation (DIC), fibrinogen deficiency, or clotting factor deficiency)	
8. Significant autoimmune disease including but not limited to immune cytopenias, rheumatoid arthritis, systemic lupus erythematosus, other connective tissue disorders, vasculitis, inflammatory bowel disease, severe psoriasis	
9. History of malignancy, except basal skin cell carcinoma	
10. Major psychiatric disorder that is not adequately controlled by treatment	
11. Epileptic seizures that are not adequately controlled by treatment	
12. Active infection, e.g., deep-tissue infection, that the Investigator considers sufficiently serious to preclude study participation	
13. In the Investigator’s opinion, is at high risk for infection (e.g., indwelling catheter, dysphagia with aspiration, decubitus ulcer, history of prior aspiration pneumonia or recurrent urinary tract infection)	
14. Seropositivity for human immunodeficiency virus (HIV)	
15. Infection with hepatitis C virus	
16. Past or present hepatitis B infection (positive hepatitis B serology)	
17. Active infection with human cytomegaly virus (HCMV), Epstein-Barr virus (EBV), varicella-zoster virus (VZV)	
18. Latent tuberculosis unless effective anti-tuberculosis therapy has been completed, or active tuberculosis.	
19. Invasive fungal infections in history and at present	
20. Cervical cytology other than PAP I or PAP II (Papanicolaou) or cervical high risk human papillomavirus (HPV) positivity	
21. Any other illness or infection (latent or active) that, in the Investigator’s opinion, could be exacerbated by study medication	
22. CD4^+^ T-cell count (absolute CD3^+^CD4^+^) < lower limit of normal (LLN) at Screening	
23. CD8^+^ T-cell count (absolute CD3^+^CD8^+^) < LLN at Screening	
24. B-cell count (absolute CD19^+^) < LLN at Screening	
25. Absolute neutrophil count < LLN at Screening	
26. Confirmed platelet count < the LLN of the evaluating laboratory at Screening or documented at <100,000/μL within the past year on a sample without platelet clumping	
27. Presence (i.e., above the ULN) of anti-thyroid stimulating hormone receptor antibodies (anti-TSHR) and anti-thyroid peroxidase antibody (anti-TPO)	
28. Any hepatic or renal function value grade 2 or higher at Screening, with the exception of hyperbilirubinemia due to Gilbert’s syndrome. See Table below, drawn from the National Cancer Institute (NCI) Common Terminology Criteria for Adverse Events v4.0 (CTCAE), published 28 May 2009.	
29. Vaccination less than 6 weeks prior to treatment with Lemtrada®.	
30. Treatment with antineoplastic or immunosuppressive drugs within 8 weeks prior to study inclusion	
31. Intolerance of pulsed corticosteroids, especially a history of steroid psychosis	
32. Inability to undergo MRI with gadolinium administration	
33. Of childbearing potential with a positive serum pregnancy test, pregnant or lactating	
34. Female patients of childbearing potential: Unwilling to agree to use a reliable and acceptable contraceptive method (Pearl index <1) throughout the study period. These methods include: hormone releasing intrauterine device (IUD), hormonal-based contraception, surgical sterilization, abstinence, or double-barrier contraception (condom and occlusive cap [diaphragm or cervical cap combined with spermicide]).	

### Interventions

After a screening period of approximately 4 weeks for determination of patient’s eligibility, included patients will be participating in the study for 36 months with alemtuzumab infusions at month 0 and 12.

Apart from clinical examination screening comprises visual, somatosensory and motor evoked potentials, optical coherence tomography, MRI scans, blood and cerebrospinal fluid (CSF) sampling. Female patients of child bearing potential are obliged to have a pregnancy test prior to each course as well as yearly endometrial smear tests and investigations for human papillomavirus (HPV). All follow-up examinations will be performed as scheduled according to the Additional file 1: Assessment Schedule.

Patients will be treated with Lemtrada® by daily IV infusions over a period of approximately 4 h in a supervised medical setting. It will be administered at a dosage of 12 mg/day for 5 consecutive days at Month 0 (60 mg total dose) and for 3 consecutive days at Month 12 (36 mg total dose). Observation for infusion-associated reactions (IARs) is recommended during and for 2 h after Lemtrada® infusion.

As an IAR precaution patients will be pre-treated with corticosteroids (1000 mg prednisolone) immediately prior to administration of Lemtrada® on each of the first 3 days of each treatment course. Additionally, pre-treatment with antihistamines and/or antipyretics prior to administration of Lemtrada® may be considered. Oral prophylaxis for herpes infection will be administered to all patients starting on the first day of each treatment course and continuing for a minimum of 1 month following treatment with Lemtrada®.

### Outcome parameters

#### Primary endpoints

Absolute and relative change from baseline of T cell subsets (CD4 and CD8 positive T cells: naïve T cells, T effector cells, T memory cells, regulatory T cells; T-helper subsets: T_h_ 1, T_h_ 2, T_h_ 17), B cell subsets (Recent bone marrow emigrants, mature naïve, memory B cells and plasma cells), natural killer cells (CD56bright, CD56dim, natural killer T cells), antigen-presenting cells (Dendritic cells: CD303^+^ plasmacytoid, CD11c^+^ and CD141^+^ myeloid dendritic cells; non-classical CD14^+^CD16^++^HLA-DR^++^, classical CD14^++^CD16^−^HLA-DR^+^ monocytes and macrophages) and myeloid-derived suppressor cells in the peripheral blood at indicated time-points of sampling are considered as primary endpoints (see Additional file 1: Assessment Schedule). A complete listing is found in Table 3.

**Table 3 Tab3:** Primary Endpoints

Absolute and relative change from baseline of the following cell counts in the peripheral blood at indicated time points of sampling (see Additional file 1: Assessment Schedule):	
a. T cell subsets:	
- CD4 and CD8 positive T cells: naïve T cells, T effector cells, T memory cells, regulatory T cells	
- T-helper subsets: T_h_ 1, T_h_ 2, T_h_ 17	
b. B cell subsets:	
- Recent bone marrow emigrants, mature naïve, memory B cells	
- Plasma cells	
c. Natural killer cells:	
- CD56bright, CD56dim	
- Natural killer T cells	
d. Antigen-Presenting cells:	
- Dendritic cells: CD303^+^ plasmacytoid, CD11c^+^ and CD141^+^ myeloid dendritic cells	
- Monocytes and macrophages (non-classical CD14^+^CD16^++^HLA-DR^++^, classical CD14^++^CD16^−^HLA-DR^+^)	
e. Myeloid-derived suppressor cells.	

#### Secondary endpoints

Secondary endpoints extend the already mentioned investigations in the peripheral blood and mainly focus on three points: The absolute and relative change from baseline of the aforementioned cell counts in the CSF at indicated time points of sampling (see Additional file 1: Assessment Schedule), functional characterization of T cells in peripheral blood and the CSF at indicated time points of sampling (see Additional file 1: Assessment Schedule) and the evaluation of potential neuroprotective properties of alemtuzumab. A complete listing is found in Table 4.

**Table 4 Tab4:** Secondary Endpoints

1. Absolute and relative change from baseline of cell-counts in the CSF at indicated time-points of sampling (see Additional file 1: Assessment Schedule). The same cell-types as indicated for the primary endpoints will be evaluated.	
2. Functional characterization of T-cells in the peripheral blood and the CSF at indicated time-points of sampling (see Additional file 1: Assessment Schedule):	
a. Activation status of cell surface receptors assessed by flow cytometry: Relative and absolute change from baseline of mean fluorescence intensity (MFI) and of proportion of positive cells regarding CD25, HLA-DR, LFA-1, CD29, CD69, CD71 expression	
b. Expression of co-inhibitory molecules assessed by flow cytometry: Relative and absolute change from baseline of MFI and of proportion of positive cells regarding PD-1 = CD279, ICOS = CD278, TIM-3, CTLA4 expression	
c. Effector functions of CD4 and CD8 positive T cells:	
- Relative and absolute change from baseline of the results of cell proliferation assays assessed as percentage of proliferated cells	
- Relative and absolute change from baseline of cytokine production measurement assessed as concentration	
- Relative and absolute change from baseline of cytolytic activity assessed by flow cytometry measurement of MFI and proportion of positive cells regarding Granzyme B, Perforin and CD107a expression	
- Relative and absolute change from baseline of intracellular calcium response assessed as concentration	
d. Migrational capacity:	
- Relative and absolute change from baseline MFI and proportion of positive cells assessed by flow cytometry expression analysis of CD11a, CD31, CD44, CD49d, CCR5, CCR6, CCR7	
- Absolute and relative change of cell numbers of migrated cells compared to baseline assessed in an in vitro model by flow cytometry analysis	
e. Spectratyping of the T cell repertoire concerning the expansion of distinct clones:	
- Relative and absolute change from baseline for complexity scores	
- Qualitative comparison of the distribution of CDR3 sequences	
f. Regulatory T-cell function:	
- Relative and absolute change from baseline in production of TGF-beta and IL-10 of CD4^+^CD25^+^FOXP3^+^ regulatory T cells	
- Suppression of T cell proliferation: Relative and absolute change from baseline in responder T cell proliferation assessed by suppression assays	

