##### Migration Assay

Transmigration assays will be performed with minor modifications as described previously [34, 35]. Briefly, transwell inserts will be assembled with HBMEC (human brain microvascular endothelial cells). Human PBMCs (each 5x105) will be transferred to the HBMEC layer for 14 h. Migrated cells from the lower of the two compartments will be collected and Calibrite beads (BD Biosciences) will be added. Next, human cells will be stained for CD4, CD8, CD14, CD19 and CD56, with the respective monoclonal antibodies and relative cell numbers will be determined by flow cytometry.

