##### Proliferation Assays

Human PBMCs will be labelled with 5 μM carboxyfluorescein succinimidyl ester (CFSE; Invitrogen) according to the manufacturer’s instructions, and proliferation will be assessed by flow cytometry after stimulation with anti-human CD3 (OKT3; 2 μg/ml) and soluble mouse anti-human CD28 (1 μg/ml; eBioscience) for 4 days.

Alternatively cell proliferation will be assessed using the ATPLite™ Luminescence Assay System (PerkinElmer) according to the manufacturer’s instructions. Luminescence will be measured on a TopCount NXT.

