## Discussion

Approved for the treatment of active RRMS alemtuzumab has demonstrated a favourable risk-benefit profile under the precautions of an intensive surveillance program. Alemtuzumab leads to a sustained reprogramming of the immune system lasting for at least several years and is associated with considerable adverse events, which necessitate the early recognition for therapy in time. For the best possible risk-benefit ratio deeper insights into the MOA are clearly needed to identify markers for treatment response and adverse event risk.

So far, the mechanism by which alemtuzumab exerts its therapeutic effects in MS is not fully elucidated. Initial clinical trials demonstrated efficiency of alemtuzumab rather in RRMS then SPMS pointing towards effects directed against acute inflammatory processes predominantly driven by adaptive immunity in contrast to neurodegenerative processes partially driven by innate immunity [40]. This is thought to be related to the limited expression of CD52 on innate immune cells leading to resistance to alemtuzumab mediated depletion. A study of Buggins and colleagues (2002) observed a loss of CD52 in tissue-resident human innate immune cells during maturation or differentiation [41]. The relatively unaffected innate immune system as well as the limited immune cell depletion in primary and secondary lymphoid tissues (as observed in humanized CD52 mice [4]) are believed to explain the low incidence of severe or opportunistic infections despite the long-lasting lymphopenia.

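### The migration endpoint counts migrated cells from a fixed number of unsorted PBMC and states no division by the T cells loaded, so near the lymphocyte nadir it can fall by about 63–85% with no change per cell

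*Protocol article*

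**What the plan says.** Table 4 (Secondary Endpoints) places items 2a to 2f under the functional characterization of T cells. Within item 2d, on migration, one endpoint is "Absolute and relative change of cell numbers of migrated cells compared to baseline assessed in an in vitro model by flow cytometry analysis".

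The Migration Assay section describes how it is obtained: "Human PBMCs (each 5x105) will be transferred to the HBMEC layer for 14 h". The input is printed as 5x105, evidently 5×10⁵ with the superscript lost. Beads are added to the cells collected from the lower compartment, then "human cells will be stained for CD4, CD8, CD14, CD19 and CD56, with the respective monoclonal antibodies". For the read-out, the section states only that "relative cell numbers will be determined by flow cytometry". It does not say what the numbers are relative to.

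The Background says that CD52 sits mainly on T and B lymphocytes and less on monocytes and macrophages. The Discussion refers to the "limited expression of CD52 on innate immune cells leading to resistance to alemtuzumab mediated depletion". The Sample size section assumes 2100 lymphocytes/µl before treatment and 100/µl after.

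Two related items stand in Table 4, item 2c, under effector functions of CD4 and CD8 T cells. Proliferation is to be expressed as the percentage of cells that have proliferated; the Proliferation Assays section first describes CFSE with flow cytometry, then adds: "Alternatively cell proliferation will be assessed using the ATPLite" luminescence system. The cytokine endpoint is "Relative and absolute change from baseline of cytokine production measurement assessed as concentration", and the Cytokine detection section names culture supernatants and CSF as the material tested.

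**The concern.** The number of T cells that migrate is the product of two things: how many T cells were put on the endothelial layer, and what fraction of them crossed. Only the fraction is migratory capacity. Fixing the PBMC number does not fix the T-cell number when treatment changes the make-up of PBMC. Lineage staining of the lower compartment shows which cells crossed, not how many of each were loaded.

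As repopulation proceeds the T-cell input changes again, so a composition effect could trace a fall and recovery that looks like functional reprogramming, a central interest of the study. The Discussion also sets this experiment against an animal study that found no effect of anti-CD52 treatment on migration. An uncorrected count could appear to contradict that study for a reason unrelated to migration.

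**Working it through.** **The plan's own figures.** No expected value is given for migration. The lymphocyte counts come from the precision calculation, where half-width = t(0.975, n−1) × SD/√n × √[χ²(0.80, n−1)/(n−1)]. For n = 15 and n = 10 this gives 283.75 and 375.44 (SD 450), 31.53 and 41.72 (SD 50), and 315.28 and 417.16 (SD 500). The article states 284 and 375, 32 and 42, 315 and 417. All six reproduce and are not affected by this point.

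**Inputs.** From the article: lymphocytes L = 2100/µl before and 100/µl after; fixed PBMC input. Assumed, not in the article: monocytes M = 200–800/µl, unchanged by treatment; PBMC = L + M; T-cell share of lymphocytes constant at first; per-cell migration constant. A count of 1000/µl is assumed for partial recovery.

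**Formula.** Lymphocyte share of PBMC = L/(L+M). With constant per-cell behaviour, apparent change = (share after ÷ share before) − 1.

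| M (/µl) | Share at 2100 | Share at 100 | Apparent fall | Share at 1000 | Apparent fall |
|---|---|---|---|---|---|
| 200 | 0.913 | 0.333 | 63% | 0.833 | 9% |
| 400 | 0.840 | 0.200 | 76% | 0.714 | 15% |
| 600 | 0.778 | 0.143 | 82% | 0.625 | 20% |
| 800 | 0.724 | 0.111 | 85% | 0.556 | 23% |

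At M = 400 and a T-cell share of 70%, T cells loaded go from 5×10⁵ × 0.840 × 0.70 = 294,000 to 5×10⁵ × 0.200 × 0.70 = 70,000.

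**If the T-cell share of lymphocytes also falls**, say from 70% to 40%, each ratio is multiplied by 4/7. At 100/µl the fall becomes 1 − 0.365 × 4/7 = 79% (M = 200) to 1 − 0.153 × 4/7 = 91% (M = 800). At 1000/µl it becomes 1 − 0.913 × 4/7 = 48% to 1 − 0.767 × 4/7 = 56%. The Background makes some such shift plausible: B cells return within 6 months, while CD4 and CD8 cells do not reach the lower limit of normal before 35 and 20 months.

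**What the undefined reference could mean:**
- Relative to beads: a count, so the effect is present in full.
- Relative to all PBMC loaded: the denominator is constant, so the effect is present in full.
- Relative to all migrated cells: the proportion still follows the composition of what was loaded.
- Relative to loaded cells of the same lineage: the change is 0% in every scenario above.

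Only the last removes the effect, and the article does not state it.

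**Proliferation.** CFSE can yield a percentage of divided cells and can be gated on CD4 and CD8. A luminescence reading of the culture yields neither a percentage nor a CD4/CD8 split.

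**The case against.** **Migrated cells are not read as one total.** They are stained for five lineages, so a reader who inferred that T cells are lumped with other PBMC would be mistaken. This stands. The gap is the missing denominator for each lineage.

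**Normalisation may exist elsewhere.** The assay is described briefly, by reference to earlier publications, and the full protocol is not shown. The relative numbers might already be per loaded lineage cell, so it cannot be said that the artefact will occur. But Table 4 does state the scale, as a change in numbers of migrated cells, and followed as written that scale mixes capacity with input.

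**Composition is measured anyway.** The primary endpoints count these subsets in blood, so a shift would be visible beside the functional result. This helps interpretation. However, the Cell Isolation section says composition is assessed on fresh cells, and the other PBMC analyses use aliquots frozen for at least 4 weeks. No step records what the thawed, loaded aliquot contains.

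**The size is a nadir figure.** Correct. Sampling times are in an additional file not shown, so the number of migration samples near the nadir is unknown.

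**The reach is limited.** Item 2d also has fluorescence-intensity and proportion-positive measures with their own per-cell scale, the calcium and suppression assays use sorted cells, and all inference is exploratory. This also stands.

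**Cytokines.** It is tempting to infer the same fault in the cytokine endpoint. The article does not support that: it does not state the cell type or number cultured, CSF is also tested, and cytokines from non-T cells need not fall.

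**Conclusion.** The point holds for the migrated-cell count in item 2d. As written, the endpoint does not separate T-cell migratory capacity from the number of T cells loaded. At the article's 2100 and 100 lymphocytes/µl the apparent fall is about 63–85% with no change per cell, assuming monocytes unchanged at 200–800/µl and a constant T-cell share. At an assumed 1000/µl it is 9–23% on the same assumptions, and larger if T cells lag behind B cells. The nadir figure should not be read as the size of the effect over the whole study.

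The ATPLite mismatch also holds, independently of these numbers, but only where that alternative is used. For cytokines, confounding by whole-PBMC culture is possible but not shown. The primary endpoints and the sample-size calculation are unaffected.

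**What to change.** - **Migration, item 2d:** define the endpoint as migrated CD4+ cells divided by CD4+ cells loaded, and likewise for CD8+, and analyse its change from baseline. Measure the composition of the thawed, loaded aliquot with the same antibodies, beads and cytometer. In the Migration Assay section, state what the relative numbers refer to.
- **Proliferation, item 2c:** use CFSE gated on CD4 and CD8 at every visit for the percentage endpoint, and do not substitute ATPLite for it.
- **Cytokines, item 2c:** state the cell type and number in the cultures. If they are unsorted PBMC, express T-cell cytokine output per T cell plated. CSF concentrations need no such division.

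The cost is one extra stain per migration sample, with the few cells it uses, and a changed formula. No additional visit, blood draw or instrument is needed.
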